### Sample size

To calculate the minimally required number of CR clinics participating in the trial, data from a previous trial (concerning the effect of CDS on guideline concordance) was used [7]. Calculations were based on the normal approximation to the binomial distribution, using a type I error risk (alpha) of 5% and 80% power. Also, we assumed that participating clinics will see 350 CR patients, on average, during the study period of 1 year, and that there will be a design effect of 23.0 due to clustering. This is based on an intra-cluster correlation coefficient (ICC) of 0.063, which is the median ICC for process variables found in 21 studies, reported by Campbell et al. [57].

In the previous study [7], CDS increased concordance with guideline-recommended therapeutic decisions for exercise training from 84.7% to 92.6%. To demonstrate a further increase to 97.6% (+5%) in the current study, at least 19 participating clinics (6,712 patients) are required under the assumptions given. For education, the concordance level previously rose from 63.9% to 87.6%. Demonstrating a further increase to 95.1% (+7.5%) requires 14 participating clinics (5,057 patients). For relaxation therapy, the previous study showed an increase from 34.1% to 59.6%, and showing an additional increase to 74.6% (+15%) requires ten participating clinics (3,517 patients). For lifestyle change therapy, finally, no significant effect of CDS was observed in the previous study (57.4% vs. 54.1%). To prove that the current intervention causes an increase from 57.4% to 72.4% (+15%) will also require that 13 clinics (3,632 patients) participate. Based on these results, we aim to include at least 19 CR clinics in our study.

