### Statistical analysis

For the primary outcome measures, we will use mixed-effect logistic regression analysis [7,58], including clinic as random effect, to assess the effect of the intervention. Included covariates will be study arm, time since study start, and time × arm interaction. We will focus on the interaction term to assess the difference in change over the study period between the two arms—that is, the effect of the intervention—because we expect concordance to improve gradually.

For the secondary outcome measures, a similar analysis will be conducted, though replacing the logistic function by another link function as appropriate. Changes in practice variation will be assessed by including a random coefficient for ‘time since study start’ in the regression model and comparing the variation in estimated quality scores before and after the study.

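### The stated 80% power is for a comparison of two fixed proportions, not for the time × arm interaction that the plan reads as the intervention effect

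*Protocol article*

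**What the plan says.** **Protocol article, Sample size.** The method is given as "Calculations were based on the normal approximation to the binomial distribution, using a type I error risk (alpha) of 5% and 80% power". The cluster size is the whole year's intake: "participating clinics will see 350 CR patients, on average, during the study period of 1 year". The clustering allowance is stated as "there will be a design effect of 23.0 due to clustering", from an ICC of 0.063. Each of the four therapies has one control proportion and one target proportion: 92.6% to 97.6% for exercise training, 87.6% to 95.1% for education, 59.6% to 74.6% for relaxation, and 57.4% to 72.4% for lifestyle change. No time course, slope or slope variance appears.

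**Protocol article, Statistical analysis.** The primary model is a mixed-effect logistic regression with clinic as random effect and fixed terms for arm, time since study start and their interaction. The effect of the intervention is defined by the interaction: "We will focus on the interaction term to assess the difference in change over the study period between the two arms". The reason given is "because we expect concordance to improve gradually". A random coefficient for time is mentioned only for the assessment of practice variation.

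**The concern.** The sizing and the primary test describe different quantities. The formula compares two levels as if every patient in the year were exposed to the full difference. The interaction compares two slopes. If the full difference were present throughout, the arm term would absorb it and the interaction would be zero. If the gain builds up gradually, the year's patients do not all carry the target difference. A straight rise on the percentage scale to +5 points at month 12 averages only 2.5 points over the year.

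At stake is whether 80% power can be claimed for the result on which the trial will be judged. Gains made before or soon after time zero also go largely into the arm term, which the plan does not read as the effect.

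**Working it through.** **1. Reproducing the plan's figures.** Design effect: 1 + (350 − 1) × 0.063 = 22.987. Patients before clustering, two-sided 5% and 80% power:

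n = [1.960 √(2 p̄(1 − p̄)) + 0.842 √(p₁(1 − p₁) + p₂(1 − p₂))]² / (p₂ − p₁)²

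For exercise training (p̄ = 0.951): (0.5983 + 0.2552)² / 0.05² = 291.4, rounded up to 292.

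| Therapy | n | n × 22.987 | Article |
|---|---|---|---|
| Exercise | 292 | 6,712 | 6,712 |
| Education | 220 | 5,057 | 5,057 |
| Relaxation | 153 | 3,517 | 3,517 |
| Lifestyle | 158 | 3,632 | 3,632 |

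All four match exactly, so the constant-difference formula is what was used. In this formula n is the number for one arm. That the results are presented as totals is a separate matter.

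**2. Power of the interaction.** Inputs: 18 clinics (Abstract), hence 9 × 350 = 3,150 patients per arm; the article's proportions. Assumptions: even entry over one year, a flat control arm, one common trend per arm. The clinic intercepts largely cancel from a slope contrast. Power is Φ(d/SE − 1.96) plus the negligible opposite tail. Here d is the difference in fitted logit slopes, and SE comes from the expected information of the logistic model.

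*Constant difference.* d = 0. With a constant proportion, the slope variance in an arm is 12/[n p(1 − p)]. For exercise this is 12/(3,150 × 0.0685) + 12/(3,150 × 0.0234) = 0.0556 + 0.1626, so SE = 0.467. Power equals alpha, 5%, for every therapy and any number of clinics.

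*Build-up, straight on the logit scale, then flat* (d/SE → power):

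| Therapy | Full by month 3 | Full by month 6 | Full at month 12 |
|---|---|---|---|
| Exercise | 0.941/0.443 → 57% | 1.342/0.425 → 88% | 1.179/0.389 → 86% |
| Education | 0.768/0.328 → 65% | 1.122/0.318 → 94% | 1.011/0.298 → 92% |
| Relaxation | 0.458/0.188 → 68% | 0.712/0.186 → 97% | 0.689/0.183 → 96% |
| Lifestyle | 0.439/0.185 → 66% | 0.686/0.183 → 96% | 0.666/0.181 → 96% |

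For the month-12 column, d is the logit difference itself: for exercise, ln(0.976/0.024) − ln(0.926/0.074) = 3.705 − 2.527 = 1.179. If the build-up is straight on the percentage scale instead, the three columns become 69–75%, 94–98% and 83–96%. With 19 clinics, SE shrinks only by √(18/19) = 0.973.

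**3. Clinic-specific trends.** If clinic slopes vary with standard deviation s, the variance becomes SE² + 2s²/9, and a valid test has 16 degrees of freedom. The documents give no s, so a range is shown for the linear rise to month 12:

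| s (logit/year, assumed) | Exercise | Education | Relaxation | Lifestyle |
|---|---|---|---|---|
| 0 | 81% | 89% | 94% | 93% |
| 0.2 | 79% | 86% | 88% | 87% |
| 0.5 | 68% | 71% | 58% | 56% |

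Example, exercise at 0.5: √(0.389² + 2 × 0.25/9) = 0.455; 1.179/0.455 = 2.59. Part of the fall from section 2 is the change from the normal to the t reference. If slope variation of 0.5 exists and the model has only a random intercept, the error is on the other side. In a simulation with 20 clinics of 350, the type I error of the interaction was about 14% for exercise and 22% for relaxation.

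**The case against.** The strongest case for the plan is that a slope test suits this intervention. A gain needs a report, a visit, an improvement plan and local actions, with a few indicators taken up per three-month cycle (Intervention). A full effect from the first day is therefore not realistic, and the 5% figure is a property of any slope test rather than a forecast. The article gives its reason for the slope in advance, and under the gradual rise it expects, power with a common trend exceeds 80%. All of this stands.

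Three further objections also stand:

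- The article does not say whether the targets are year averages or end-of-year levels. It therefore cannot be said that the two sections strictly exclude each other. Constancy is implied by the formula and is not stated.
- The text available does not date the first report relative to time zero, and the study-flow figure is not visible here. If the first report came at month 3 (an assumption), the first quarter would act as baseline. A full, lasting jump at that point would then give 98–99% power.
- Pre-study records may not exist in every clinic, or may follow an older guideline version, so adding a baseline period cannot be called free.

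None of this supplies a power figure for the interaction or an allowance for clinic-specific trends.

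**Conclusion.** The point holds in a limited form. The stated 80% belongs to a test the plan does not use as its primary one. The actual power depends on the build-up shape, the timing of the first report and the variation in clinic trends, none of which enters the sizing. Under a common trend it falls below 80% mainly when most of the gain arrives within about the first quarter. With slope variation at the upper end of the assumed range, it falls below 80% even for the linear rise.

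A reader might infer that the trial has almost no power, or that a fast and lasting improvement would be reported as no effect. The documents do not support either. Power is high under the gradual rise the article expects. A three-month build-up would be missed in roughly a third to two fifths of trials (32–43%, from the 57–68% above), not always. These figures rest on 18 clinics of equal size, even entry, a flat control arm and assumed slope SDs.

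**What to change.** Recompute and restate power for the time × arm contrast. State the build-up shape, the date of the first report relative to time zero, and a range of clinic slope variances. Put a random slope for time in the primary model.

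Pre-specify a supporting analysis that reports the model-based between-arm difference in level, for example at month 12 or averaged over the year. A year average measures about half the target under a linear rise, so it should be labelled as a different quantity. Use pre-intervention patient records as a baseline period only where they exist under the same guideline version.

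The cost is a new calculation and a little more analysis, with no new patients or visits for the core change. The downside is a power figure that depends on the assumed shape and may be less favourable than 80%.

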**Table 3 Tab2:** **Quality indicator set for cardiac rehabilitation per study arm**

**Study arm**	**Nr**	**Type**	**Quality indicator**
A	1	Structure	Specialized education for patients with chronic heart failure
	2a	Process	Complete data collection during needs assessment for rehabilitation (concerning psychological and social functioning, and lifestyle factors)
(Patient education, quality of life, and lifestyle change therapy [ex. physical activity])			
	3	Process	Patients receive a discharge letter to stimulate continuation of lifestyle changes at home
	4	Outcome	Patients quit smoking
	5	Outcome	Patients improved their quality of life during rehabilitation
B	2b	Process	Complete data collection during needs assessment for rehabilitation (concerning physical functioning and, cardiovascular risk factors)
(Exercise training and physical activity, relaxation and stress management, cardiovascular risk factors, and work resumption)			
	6	Process	Cardiovascular risk factors are evaluated after rehabilitation
	7	Outcome	Patients improve their exercise capacity during rehabilitation
	8	Outcome	Patients meet the physical activity norms
	9	Outcome	Amount of time needed to start resumption of work
A and B	10	Structure	Rehab professionals work with a multidisciplinary patient record
	11	Structure	Long-term patient outcomes are assessed
	12	Structure	Patients participate in patient satisfaction research
	13	Structure	Clinics perform internal evaluations and quality improvement
	14	Process	Average time between hospital discharge and start of rehabilitation
	15	Process	Patients are offered a rehabilitation program tailored to their needs
	16	Process	Patients finish their rehabilitation program
	17	Process	Rehabilitation goals are evaluated afterwards
	18	Process	Cardiologists receive a report after the rehabilitation

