### Participants

#### Inclusion criteria (clinic level)

All CR clinics that use an EPR for CR with CDS during the CR needs assessment procedure and that are willing to dispose their data for research and to set up a QI team are eligible to participate in the study. There are 91 CR clinics in the Netherlands, the majority affiliated with hospitals [42]. Twelve clinics are located in specialized rehabilitation centers [42], who have regional functions and can treat simple but especially more complex referred patients. Both types of clinic work according to the same guidelines and are eligible to participate in the study.

In the Netherlands, there are two commercial vendors of CDS systems for CR that can be used for data collection. Both systems have been validated for their advice being completely consistent with the guidelines. Also data collection in these systems is in line with the minimal dataset of our study. The minimal dataset is based on the set of 18 quality indicators for CR (see Table 3) and consists of (i) patient identification data (31 items), (ii) CR needs assessment data (80–130 items, see Table 4), (iii) data on selected rehabilitation goals and therapies (79 items), and (iv) CR evaluation data (105 items). Clinics that use one of the CDS systems automatically collect the right data items. The price of both systems depends on contract conditions, but amounts on average to €20,000 for purchase and to €4,000 per year for service, updates, and maintenance.

**Table 4 Tab4:** **Items which need to be measured during the needs assessment procedure according to recommendations in the Cardiac Rehabilitation Guidelines** [26,38]

**Domain**	**Item**	**Clinical algorithm cardiac rehabilitation 2012**
1. Physical functioning	Objective exercise capacity	Maximal symptom limited exercise tolerance test.
		For patients with heart failure: completed with a spiroergometry (VO2max) test [43].
	Subjective exercise capacity	MacNew Quality-of-Life questionnaire (27 questions) [44,45]
2. Psychological functioning	Emotional function	MacNew Quality-of-Life questionnaire (27 questions) [44,45]
	Anxiety and Depression	Option 1: Generalized Anxiety Disorder scale (GAD-7, 7 questions) [46] in combination with the Patient Health Questionnaire (PHQ-9, 9 questions) [47]
		Option 2: Beck Anxiety Inventory (BAI, 21 questions) [48] in combination with the Beck Depression Inventory (BDI, 21 questions) [49]

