		Option 3: Hospital Anxiety and Depression Scale (HADS, 14 questions) [50]
3. Social functioning	Social function	MacNew Quality-of-Life questionnaire (27 questions) [44,45]
	Social support	Option 1: Multidimensional Perceived Social Support Scale (MPSSS, 12 questions) [51,52]
		Option 2: ENRICHD Social Support Inventory (ESSI, 7 questions) [53]
	Life Partner	Clinical interview (3 questions)
	Resumption of work	Clinical interview (10 to 18 questions)
4. Cardiovascular risk profile	Cardiovascular risk profile	Physical examination (obesity, blood pressure), blood testing (cholesterol and diabetes)
5. Lifestyle factors	Smoking status	Clinical interview (1 to 4 questions) and specific treatment advice
	Physical activity	Monitor ‘Physical activity and Health’ (4 questions) [54]
	Dietary habits	Individual screening by dietician (in case of hypertension, hypercholesterolemia, obesity, or diabetes)
	Alcohol consumption	Five Shot questionnaire (5 questions) [55,56]

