## Appendix I

### Rules to set icon colors in CARDSS Online

- Structure (yes or no) indicators: The value ‘yes’ is considered acceptable (green), the value ‘no’ borderline (orange) if less than 50% of all clinics has yes, and poor (red) if more than 50% has yes.
- Frequency indicators (percentages): The interpretation is depending upon the mean value of all clinics. If this mean value is less than 66%, a value above 66% is considered acceptable (green); a value between 33% and 66% or a value up to 10% less than the value of all clinics is considered borderline (orange); and all other values are considered poor (red). If the mean value off all clinics is above 66%, a value up to 10% less than the value of all clinics is considered acceptable (green); a value above 33% is considered borderline (orange); and all other values are considered poor (red).
- Numeric non-frequency indicators (e.g., average increase in exercise capacity before and after the rehabilitation): Thresholds were determined by consulting the prevailing guidelines where possible, and otherwise based on observed distributions in previous studies or determined by consulting clinical experts. Also they depend on the mean value of all clinics. For instance, an average increase in exercise capacity above 10% is considered acceptable (green) if the mean value of all clinics is not above 20%; between 0% and 10% as borderline (orange) if the mean value of all clinics is not above 20%; and all other values, e.g., a decrease in exercise capacity, are considered poor (red).

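### The stated model does not adjust the quality-of-life, exercise-capacity and physical-activity indicators (5, 7, 8) for the patient's intake level, although that level is measured

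*Protocol article*

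**What the plan says.** For the primary outcome, the Statistical analysis section of the protocol article specifies a mixed-effects logistic model with clinic as a random effect. It lists the fixed terms: "Included covariates will be study arm, time since study start, and time × arm interaction". The effect is read from the interaction: "We will focus on the interaction term to assess the difference in change over the study period between the two arms". The secondary outcomes follow the same scheme: "For the secondary outcome measures, a similar analysis will be conducted, though replacing the logistic function by another link function as appropriate". The link function is the only change named.

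Three of the outcome indicators in Table 3 have a counterpart at intake:

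- Indicator 5 (arm A): "Patients improved their quality of life during rehabilitation". Table 4 lists the MacNew questionnaire at the needs assessment.
- Indicator 7 (arm B): "Patients improve their exercise capacity during rehabilitation". Appendix I describes it as an "average increase in exercise capacity before and after the rehabilitation". Table 4 lists a "Maximal symptom limited exercise tolerance test" at the needs assessment.
- Indicator 8 (arm B): whether patients meet the physical activity norms. Table 4 lists a four-question physical activity monitor at the needs assessment.

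The minimal dataset also holds 105 evaluation items, so both ends of the rehabilitation period are recorded.

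**The concern.** Where a patient ends up depends on where that patient started, and so does the size of the improvement: low starters have more room to gain and high starters may reach a ceiling. A model without the intake level leaves this predictable variation in the residual. The tested slope difference is then noisier than the collected data require.

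The second issue is protection against a changing intake. Patients enter over a year, after their clinic has been allocated, in clinics that cannot be blinded, and only about 18 clinics are randomised. If the intake level moved differently in the two arms, the unadjusted time × arm term would absorb part of that movement.

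The Strengths and limitations section relies on the full indicator set to show the direct relation between the intervention and changes in performance, so these analyses carry some weight.

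**Working it through.** **Inputs from the documents.** 350 patients per clinic, alpha 5%, 80% power and ICC 0.063 (Sample size section); 18 clinics (Abstract). The stated design effect reproduces: 1 + 349 × 0.063 = 22.987, given as 23.0. The article states no power or sample size for indicators 5, 7 or 8, so there is no figure of its own to reproduce for them.

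**Assumptions.** Nine clinics per arm; uniform entry over the year; two-sided test; both values known for all patients; equal SDs at intake and follow-up; intake/follow-up correlation r = 0.5, range 0.3 to 0.7 (the documents give none); indicator 8 assessed after rehabilitation.

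**Step 1: variance.** Per patient, in units of the variance of one measurement:

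- follow-up value alone: 1
- change: 2(1 − r)
- either one adjusted for intake: 1 − r²

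For a continuous outcome, adjusting the change for intake gives the same arm and time effects as adjusting the end value. The ratios, adjusted to unadjusted, are therefore (1 − r²)/[2(1 − r)] = (1 + r)/2 for a change and 1 − r² for an end value.

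**Step 2: power.** A contrast with 80% power has a true effect of 1.960 + 0.842 = 2.802 standard errors. With variance ratio f, power becomes Φ(2.802/√f − 1.960).

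| r | f, change | power | f, end value | power |
|---|---|---|---|---|
| 0.3 | 0.65 | 93.5% | 0.91 | 84% |
| 0.5 | 0.75 | 90% | 0.75 | 90% |
| 0.7 | 0.85 | 86% | 0.51 | 97.5% |

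A simulation of 18 × 350 patients at r = 0.5 gave 80% unadjusted and 90% adjusted (1,500 runs).

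**Step 3: what shrinks the gain.**

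- *Clinic-specific trends.* Adjustment reduces only the patient-level part. If clinic slopes supply half of the variance, f = 0.5 + 0.5 × 0.75 = 0.875 and power is 85%. If the slope variance equals the intercept variance implied by the ICC, it is 0.063/0.937 = 0.067, against 12/350 = 0.034 for patients. The patient share is then about 34%, f = 1 − 0.34 × 0.25 = 0.915, and power is about 83%.
- *Yes/no scoring.* If an underlying correlation r is cut at the median at both times, the status correlation is (2/π)·arcsin(r): 0.33 at r = 0.5 and 0.49 at r = 0.7. Using 1 − correlation² as an approximation, f is 0.89 and 0.76, and power about 84% and 90%.
- *Type of contrast.* The gain exists because the test is on a within-clinic slope. In a plain arm-level comparison, patient-level variance would be only 0.937/22.987 = 4% of the total, and the gain negligible.

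**Step 4: drift.** Let the intake level in one arm move by D SD relative to the other over the year, with no treatment effect. The time × arm estimate is then off by +rD for an end value, −(1 − r)D for a change (opposite in sign to the drift), and 0 after adjustment. A drift shared by both arms gives D = 0 and no bias in any of the three.

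For illustration at r = 0.5, D = 0.2 gives +0.10, −0.10 and 0; simulation agreed. The standard error of the slope difference is √(2 × 12/(9 × 350)) = 0.0873 SD. The bias is thus 0.10/0.0873 = 1.15 standard errors and the false-positive rate about 21%. At D = 0.1 it is about 9%, and at D = 0 it is 5%. No value of D other than zero comes from the documents.

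**The case against.** The strongest case against has four parts.

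- *This is a condensed article, and outcome-specific covariates belong in the analysis plan.* That plan may indeed add them, which limits the weight of the point. But the article lists the covariates and names the link as the only change. It is fair to comment on the model as stated.
- *Indicators 5 and 7 already use the intake value.* Correct. A reader might infer that all three indicators are analysed without it. That describes only indicator 8. For 5 and 7, what is absent is adjustment of the change for its starting level.
- *The bias is hypothetical.* A reader might infer that any drift in intake status would pass for an intervention effect. The documents do not support that: the time term absorbs a common drift, all consecutive patients are included, and clinics are randomised within size strata. The admission in the limitations that patient mix is not corrected concerns the feedback to clinics, not the trial analysis. What remains is an unprotected route to bias, of unknown size.
- *The precision gain is optimistic and the remedy has costs.* Partly right. The plan itself fits a random coefficient for time when it studies practice variation, so clinic trends may well differ, and indicator 8 is a yes/no status. Requiring an intake value for indicator 8 could also exclude patients unevenly, because complete intake data is itself a feedback target that differs by arm (indicators 2a and 2b). Replacing improvement by the end value would redefine indicators chosen by consensus. These objections shape the remedy. They do not remove the case for it.

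**Conclusion.** The point holds in limited form. The model as stated does not adjust indicators 5, 7 and 8 for an intake level that the needs assessment already measures.

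The firm part is lost precision. At r = 0.5, patient-level variance with adjustment is 0.75 of that without, for a continuous outcome analysed as a within-clinic trend. The corresponding power is 90% against 80% at best, and about 83% to 85% with varying clinic trends or a yes/no indicator. All of this rests on an assumed correlation.

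The bias part is conditional: only drift that differs between arms matters, and its size is unknown. The false-positive rates above show how sensitive the test is. They do not predict what this trial will see.

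The primary outcome is unaffected. The change is worth making because it is cheap, not because the secondary analyses would otherwise be invalid.

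**What to change.** Keep the indicator definitions and add one sentence to the Statistical analysis section, for example:

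*For indicators 5, 7 and 8, the model also includes, as a patient-level covariate, the same measure at the needs assessment (MacNew score, exercise capacity or physical activity, respectively), beside study arm, time and time × arm. Patients without an intake value are retained, by a method stated in advance.*

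Imputation or a missing-value indicator would serve for indicator 8. For indicators 5 and 7, a patient without an intake value has no computable change in any case, so the covariate excludes nobody further; imputation would be needed to bring such patients in. Retention matters because completeness of intake data is promoted differently in the two arms (2a and 2b).

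No new data are needed, and the figures shown to clinics stay as they are. The costs are the missing-intake rule, which is new for indicator 8, and an odds ratio that is conditional on intake level wherever an indicator is analysed as binary.
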